## Participants

### Enrollment Goal

40 participants with SCI.

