### *Visit 3 /Baseline EMG Mapping of Spinal Cord Segments with TCSCS / Week 3-4*

Approximately 2 hours.

Participants will undergo baseline mapping using surface EMG (Delsys Inc., Natick, USA) and concentric needle EMG as per an established protocol to record muscle activation during transcutaneous spinal cord stimulation (mapping) (TESCoN, SpineX Inc., CA, USA) at different spinal cord levels and different intensity. Please see subsections entitled TCSCS, Surface EMG and Concentric Needle EMG in Descriptions of Assessments section for details.

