### *Visits 4,5,6: Urodynamics and Anorectal Manometry – Weeks 4-6:*

Approximately 2.5 hours per visit.

Following Visits 1 (Screening) Visit 2 (baseline assessments) and Visit 3 (mapping visit) using a randomized counter-balanced approach, all individuals will be allocated into two distinct pathways:

- Pathway #1: individuals will start with Urodynamics, (UDS 1, Visit 4), followed by a second session of Urodynamics (UDS 2, Visit 5), and ARM (Visit 6).
- Pathway#2: individuals will start with ARM (Visit 4), followed by Urodynamics (UDS 1, Visit 5), and a second session of Urodynamics (UDS 2, Visit 6)).

TCSCS and Cardiovascular monitoring will be performed during UDS and ARM. Please see Description of Assessments for details of Urodynamics, ARM, TCSCS and Cardiovascular monitoring.

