### *Visits 7 – 18 or 36: Long Term TCSCS – Weeks 7-12:*

Approximately 90 minutes per visit.

Participants will come to ICORD for long term TCSCS, either 2 days/week (moderate) or 5 days/week (intense) for 6 weeks for a total of either 12 sessions or 30 sessions. Please see Description of Assessments for the details of an individual session.

During the 6 weeks of long term TCSCS, TNFBM will be measured during participants' conventional bowel routines at home. Participants will be asked to record the time from 'suppository insertion' to 'when bowel evacuation is completed' once per week for the bowel movement completed mid-week during each week of the 6 week TCSCS pathway.

24 ABPM will be performed mid-way through the 6 weeks and during the final week of the 6 weeks of treatment in combination with the participants' bowel routine.

## Visit 19-20 OR 37 – 38: Immediate Post-TCSCS Assessments – Week : 13

Visit 19 or 37 (approximately 3 hours):

After the 6 weeks of TCSCS, all participants will complete 1 visit at ICORD including UDS assessments and a SCI severity assessment (ISNCSCI). Please see description of Assessments for details.

Visit 20 or 38 (approximately 1 hour):

A series of questionnaires on low urinary tract function, bowel function, cardiovascular function and sexual health will be conducted by telephone or video conference call (considering the present COVID-19 pandemic environment). The questionnaires are listed below and details can be found in the Description of Assessments Section.

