### Urodynamics

Participants will undergo standard clinical procedures for UDS, including cystometry with water at 21°C and a filling rate of < 30 mL per minute through a 6F double lumen catheter with the participants in the supine position. Abdominal pressure will be measured with a 10F intrarectal balloon catheter. Pelvic floor electromyography will be recorded during cystometry with a surface electrode placed on the

perineum. Filling will be stopped when the participants report a sensation of fullness, at the moment of urine leakage, if blood pressure reaches levels of 180/110 mmHg, or per the request of the patient.

Following the standard clinical assessment UDS we will perform UDS with TCSCS. To assess the efficacy of short-term TCSCS' on LUT function, we will first prefill the bladder (i.e. 50-75% of cystometric capacity from the first UDS) without eliciting detrusor overactivity or autonomic dysreflexia. Then, TCSCS (as described above) will be delivered for 60 s each interspersed with 30 s rest (i.e. no stim) to optimize the configuration for each individual. Stimulation frequency and location will be guided by the results of the Baseline EMG Mapping of Spinal Cord Segments performed during visit 3.

TCSCS will be stopped when the participants report a sensation of fullness, at the moment of urine leakage, if blood pressure reaches levels of 180/110 mmHg, or per the request of the patient.

Urodynamics will be performed by a trained clinician (MD or RN) under the supervision of [name] (MD), who is a urologist.

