### Long Term TCSCS Visits

Each session will last approximately 90 minutes. TCSCS will be delivered using a non-invasive central nervous system stimulator (TESCoN, SpineX Inc., CA, USA). A self adhesive round electrode placed on the skin between spinous processes at the midline over the vertebral column will function as a cathode, and two rectangular self-adhesive electrodes located symmetrically on the skin over the iliac crests as anodes. Specific areas for electrode placement will be examined and prepared to reduce skin impedance. A temperature probe will be positioned adjacent to the cathode in order to monitor changes in skin temperature to prevent potential skin damage. Blood pressure and heart rate will be measured once every minute throughout the. TCSCS will be delivered under the supervision of either [name] or [name], who are both Physical Medicine and Rehabilitation physicians.

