- With TCSCS we do not expect adverse events as our study will only utilize parameters and electrodes approved in previous studies. Stimulation could potentially irritate the skin, so we will monitor skin temperature for potential irritation. TCSCS elicit AD, however so far no AD/OH is observed in TCSCS studies. Furthermore, cessation in stimulation immediately reduces blood pressure, and we will be monitoring blood pressure closely during procedures. In case of adverse

events, the participant's primary physician would be notified as needed. Participants will be continuously monitored for any signs of risks or discomfort. As mentioned, we will also continuously monitor cardiovascular signals such as blood pressure and heart rate. For TCSCS, we will additionally measure skin temperature.

- In this study, participants will be asked to undergo UDS, a clinically approved procedure for examination of urinary bladder function in participants with injury to the central or periphery nervous system. This procedure is typically recommended to be performed on a biannual basis in participants with multiple sclerosis, stroke, and SCI, in order to establish urine bladder function. It is known that within the SCI population, UDS commonly elicits episodes of AD in participants with injury at the T6 spinal segment and above (an inclusion criteria for the present study). Clinically, UDS is an important component of bladder function evaluation following SCI. Risk management in this study involves having trained personnel performing these studies in a clinical facility with protocols in place to manage iatrogenic/artificially induced episodes of AD. All these criteria are in place at the site of the Principal Investigator, located at the ICORD/Blusson Spinal Cord Injury Centre at the Vancouver General Hospital.
- Concentric needle EMG is a common clinical procedure, performed in a variety of clinical settings worldwide. The risks of EMG are very small and include small risk of bleeding, bruising and mild discomfort that can last up to 24 hours. EMG is very well tolerated and the risks will be minimized by localizing the target muscles using well-established surface anatomical landmarks in order to avoid placement in proximity to blood vessels or nerves. In the event of discomfort during the procedure, this will be minimized simply by moving the needle to a slightly different position.

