#### Treatment

Non-pharmacological components for management of AD episodes include the following:

1. When an episode of AD is confirmed, the first recommended step is to sit the participant upright or elevate the head of the bed in an attempt to induce an orthostatic decline in blood pressure. Additionally, loosen or remove all restrictive clothing and devices that could be triggers of painful stimuli (tight belt, shoe lace, orthotics on the leg, etc).
  - After this step measure blood pressure - this step could be sufficient to eliminate the episode of AD. If blood pressure is still elevated go to step 2.
2. Check the urinary bladder. If the catheter is inserted or kinked; establish urine outflow.

- After this step measure the blood pressure again and if the blood pressure is still elevated go to step 3.
3. Check for possible fecal impaction (use lidocaine gel to decrease irritation).
    - After this step measure the blood pressure again and if the blood pressure is normalized and symptoms subside, AD is successfully managed.
    - However, if arterial blood pressure is still elevated and it is above 150 mmHg the next step in management is initiation of pharmacological agents.

Based on literature and recommendations, the present pharmacological arsenal for management of AD episodes in North America includes the following:

1. Nifedipine (5mg capsule)
2. Captopril (25mg capsule)
3. Nitrates (1-2 inches applied to non-hairy part of chest)

These recommendations were developed and based on the consensus of specialists who were involved in development of PVA guidelines for management of AD following SCI.

The costs of all tests, examinations, and medical care required as a part of this study will be provided at no cost to the study subject. The subject and others may benefit from the overall conclusions to be drawn from the results of this study. Participation in this study could provide further data on the impact of TCSCS on lower urinary tract, bowel and sexual function following SCI.

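### The protocol gives conflicting instructions on whether and when stimulation stops for raised blood pressure, and only the urodynamics section contains a written pressure trigger

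*Protocol*

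**What the plan says.** Eight places in the protocol bear on this point.

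- **Cardiovascular monitoring** defines AD as a systolic rise of 20 mmHg or more over baseline and gives it as an example of an ACVE, which the abbreviation list expands as an adverse cardiovascular event. The section is written for urodynamics (UDS) and anorectal manometry (ARM) and refers AD to an established clinical management protocol.
- **Known Study Risks/Harms, first bullet**, has a broken sentence whose evident sense is that the testing session stops immediately if an adverse event occurs.
- **Known Study Risks/Harms, stimulation bullet**, links TCSCS with AD in wording that has lost a verb, notes that none has been seen in TCSCS studies so far, and adds: "cessation in stimulation immediately reduces blood pressure, and we will be monitoring blood pressure closely during procedures". It goes on to speak of continuous cardiovascular monitoring.
- **Urodynamics** ends stimulation on fullness, on leakage, or "if blood pressure reaches levels of 180/110 mmHg, or per the request of the patient".
- **Treatment** (under Managing episodes of AD) begins: "When an episode of AD is confirmed, the first recommended step is to sit the participant upright or elevate the head of the bed". It then goes to the bladder, the bowel and, if pressure is still raised and above 150 mmHg, to drugs. No step mentions the stimulator.
- **Long Term TCSCS Visits** says: "Blood pressure and heart rate will be measured once every minute throughout the". The sentence breaks off there, and no action is attached to the readings. A physician supervises.
- **TCSCS** (under Procedures), the general text that also serves mapping, sets no pressure at which stimulation ends.
- **ARM** refers back to that general text and adds no pressure trigger.

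**The concern.** Read together, these sections can prescribe different actions for the same participant at the same pressure. One appears to end the session at the first adverse event, one lets stimulation continue until a much higher pressure, and one leads to drug treatment without saying whether stimulation is still on. The protocol itself points to switching off as something that lowers pressure at once, yet the stepwise sequence does not mention it.

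This matters because every participant has an injury at or above T6, the group in which the protocol says UDS commonly elicits AD. The background section asks that any stimulation below the injury be evaluated for cardiovascular safety, and Objective 3 asks whether the six-week course is safe. Most stimulation visits fall in that six-week phase, where the text sets readings but no response to them.

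**Working it through.** **Step 1. The rules side by side.**

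| Section | Pressure finding | Action on stimulation | Applies to |
|---|---|---|---|
| Cardiovascular monitoring | Systolic rise of at least 20 mmHg = AD, an example of an ACVE | None stated; management protocol | UDS, ARM |
| Known Study Risks/Harms, first bullet | Any adverse event | Session stopped immediately | Testing session; reach to treatment visits unstated |
| Urodynamics | 180/110 mmHg | TCSCS stopped | UDS |
| Treatment | Still raised and above 150 mmHg, after three steps | None stated; drugs | AD generally |
| TCSCS (Procedures), ARM | None | None | Mapping, ARM |
| Long Term TCSCS Visits | None; read once a minute | None | Treatment visits |

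**Step 2. Where the rules part.** The 20 mmHg criterion is relative and the other two are absolute. The protocol gives no baseline pressures, so I express the comparison by baseline systolic pressure. I take 150 mmHg as systolic, which the Treatment section does not state.

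- AD is reached before 180 systolic whenever baseline is below 180 − 20 = 160 mmHg.
- AD is already present at 150 systolic whenever baseline is at or below 150 − 20 = 130 mmHg.

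Take a participant with baseline at or below 130 whose systolic pressure during UDS lies above 150 and below 180. AD is present. If AD counts as an adverse event, the first bullet ends the session. The systolic part of the urodynamics limit has not been reached. If pressure stays raised through the three non-drug steps, the Treatment section proceeds to drugs. Either AD is not an adverse event for the purpose of the general stop, or that stop and the urodynamics limit conflict. The text does not say which.

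**Step 3. How many stimulation visits have a written pressure trigger of their own.** Inputs:

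- Long-term sessions: "either 2 days/week (moderate) or 5 days/week (intense) for 6 weeks for a total of either 12 sessions or 30 sessions". Check: 2 × 6 = 12 and 5 × 6 = 30. These agree with the visit numbering, 18 − 7 + 1 = 12 and 36 − 7 + 1 = 30.
- Pre-treatment stimulation visits: one mapping visit (Visit 3), plus two UDS visits and one ARM visit (Visits 4 to 6), where "TCSCS and Cardiovascular monitoring will be performed during UDS and ARM". Total 1 + 2 + 1 = 4.
- Visits with a written pressure trigger: the two UDS visits.

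Share without one = (long-term + mapping + ARM) / (long-term + 4):

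- Moderate: (12 + 1 + 1) / (12 + 4) = 14/16 = 87.5%.
- Intensive: (30 + 1 + 1) / (30 + 4) = 32/34 = 94.1%.

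The protocol does not say whether the Week 13 UDS includes stimulation. If it does, the urodynamics trigger covers one more visit, and the shares become 14/17 = 82.4% and 32/35 = 91.4%.

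**Step 4. Monitoring frequency.** The stimulation bullet describes continuous cardiovascular monitoring. Beat-by-beat measurement is specified for UDS and ARM, and the long-term text gives one reading a minute. The general statement and the long-term text do not match.

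**The case against.** The strongest reply is that a study-wide stop already exists. The first risk bullet opens with the whole period of study. AD is an adverse cardiovascular event in the protocol's own terms, so AD would end any session, long-term ones included, and a physician is supervising. The Treatment text also summarises general consensus guidance for AD after spinal cord injury, and such a summary would not be expected to name a study device. A session stop could operate alongside it.

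Much of this stands, and it rules out several stronger readings that a reader might draw:

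- **That long-term sessions run with no safeguard.** The documents do not show this. The general stop and physician supervision may cover them. What is missing is a written pressure trigger and a clear statement of the general stop's reach.
- **That the protocol relies on switching off as its remedy for AD.** The sentence is added as reassurance. For UDS and ARM, the named means of resolving AD is the management protocol.
- **That 84% of sessions are unprotected.** With 20 participants on each schedule, (20 × 12 + 20 × 30) / (840 + 40 × 4) = 840/1000 = 84%. But this is only the share of sessions that are long-term. It needs an equal split that the protocol does not state, and it treats mapping and ARM as covered when neither has a trigger.
- **That operator-chosen stopping biases the comparison of schedules.** The protocol defines no in-session endpoint for the length or height of an episode. AD severity is defined only for the 24-hour ambulatory recording.

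The reply does not remove the conflict itself. If the general stop does apply to AD, it disagrees with the urodynamics limit wherever AD arises below that limit. If it does not, the mapping, ARM and long-term visits have no written pressure-based stop.

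**Conclusion.** The concern holds as an inconsistency: the protocol does not settle whether and when TCSCS stops for raised blood pressure. It is more than missing detail, because rules that are written down lead to different actions at one pressure in a population prone to AD.

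Of stimulation visits, 87.5% (moderate) and 94.1% (intensive) have no written pressure trigger of their own. A pooled figure would lie between these and depends on an allocation ratio that is not given. The counts assume that every scheduled visit takes place and that the Week 13 UDS is done without stimulation. They measure a gap in the text, not AD risk. If the general adverse-event stop is confirmed to cover treatment, mapping and ARM visits and to include AD, none of these visits is without a stop rule. The conflict with the urodynamics limit would then remain to be resolved.

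**What to change.** Reconcile TCSCS (Procedures), Urodynamics, Cardiovascular monitoring, ARM, Long Term TCSCS Visits, both bullets of Known Study Risks/Harms, and Treatment, so that they agree on four matters:

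1. whether the general adverse-event stop covers mapping, ARM and long-term visits as well as testing sessions, with the broken sentence repaired;
2. how AD as defined relates to that stop and to the urodynamics limit;
3. where stopping stimulation stands relative to the AD treatment sequence;
4. which monitoring frequency applies in long-term sessions, with the unfinished sentence completed.

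The pressure level and the order of steps are for the clinical team. No threshold or clinical rule is proposed here. The cost is protocol wording, with no added visits or procedures.

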#### Managing episodes of AD:

The present concept of management of AD following SCI consists of preventative and treatment strategies.

#### Prevention

Adherence to the bladder protocol and prevention of urinary tract infections is highly recommended as up to 90% of episodes of AD are related to the urogenital tract. Adherence to proper bladder management and regular bowel protocols is also highly recommended in order to prevent most common triggers of AD. Skin checkup and toenail care are crucial for participants with SCI as skin issues are among frequent triggers of AD episodes.

#### Treatment

Non-pharmacological components for management of AD episodes include the following:

1. When an episode of AD is confirmed, the first recommended step is to sit the participant upright or elevate the head of the bed in an attempt to induce an orthostatic decline in blood pressure. Additionally, loosen or remove all restrictive clothing and devices that could be triggers of painful stimuli (tight belt, shoe lace, orthotics on the leg, etc).
  - After this step measure blood pressure - this step could be sufficient to eliminate the episode of AD. If blood pressure is still elevated go to step 2.
2. Check the urinary bladder. If the catheter is inserted or kinked; establish urine outflow.

- After this step measure the blood pressure again and if the blood pressure is still elevated go to step 3.
3. Check for possible fecal impaction (use lidocaine gel to decrease irritation).
    - After this step measure the blood pressure again and if the blood pressure is normalized and symptoms subside, AD is successfully managed.
    - However, if arterial blood pressure is still elevated and it is above 150 mmHg the next step in management is initiation of pharmacological agents.

Based on literature and recommendations, the present pharmacological arsenal for management of AD episodes in North America includes the following:

1. Nifedipine (5mg capsule)
2. Captopril (25mg capsule)
3. Nitrates (1-2 inches applied to non-hairy part of chest)

These recommendations were developed and based on the consensus of specialists who were involved in development of PVA guidelines for management of AD following SCI.

The costs of all tests, examinations, and medical care required as a part of this study will be provided at no cost to the study subject. The subject and others may benefit from the overall conclusions to be drawn from the results of this study. Participation in this study could provide further data on the impact of TCSCS on lower urinary tract, bowel and sexual function following SCI.

#### Ethical and Regulatory Considerations

##### Good Clinical Practice (GCP) Statement

The sponsor investigator recognizes that it is his responsibility to ensure that this clinical study will be conducted in accordance with the ethical principles that have their origin in the Declaration of Helsinki, and that are consistent with the International Conference of Harmonization (ICH) guidelines for GCP and applicable regulatory requirements.

##### Informed Consent

The principles of informed consent described in the ICH Guidelines for GCP will be followed when enrolling participants into this study. The Informed Consent Form (ICF) used in this study must be reviewed and approved by UBC Clinical Research Ethics Board (UBC CREB).

Written informed consent will be obtained from each participant prior to their participation in any study procedure. The original ICF will be retained in the participant's study record and a copy of the signed ICF will be given to the participant. The same protocol applies to any amendments to the original consent; all versions of signed consents will be kept for the Health Canada regulated period of 25 years.

##### Participant Confidentiality and Data Protection

The investigator will take all appropriate measures to ensure that the anonymity of each study participant will be maintained. Participants will be assigned study specific numbers and study specific initials that are not based on any personal identifiers. The identification key linking participants to their study identifiers will be kept in strict confidence and access restricted to appropriate study personnel.

The investigator will take all appropriate measures to safeguard and prevent access to this information by any unauthorized third parties. However, research records and health or other source records identifying you may be inspected in the presence of the Investigator or his or her designate, by representatives of Health Canada, and the UBC Clinical Research Ethics Board for the purpose of monitoring the research. No information or records that disclose participants identity will be published without their consent, nor will any information or records that disclose participant identity be removed or released without their consent unless required by law.

